## Abstract

Background: Intimate Partner Violence (IPV) is a major public health problem that affects one-third of women aged 15 around the world. Interventions for IPV victims are essential for women’s self-esteem and self-concept recovery. This project aims to assess the effects of an eight-session multicomponent intervention program based on group psychological therapy and adventure activities in (1) self-esteem, (2) self-concept, (3) body image, (4) self-efficacy and (5) depression symptomatology in IPV victims. Methods/Design: A single-blind, randomized controlled pilot study, with experimental and control group, will be carried out. 34 IPV female victims will be recruited and equally assigned to the experimental (*n* = 17) or the control (*n* = 17) group. Primary outcome measures will include self-esteem, while secondary measures will be focused on self-concept, body image, self-efficacy, and depressive symptoms. Intention to treat and efficacy statistical analyses will be also performed. Discussion: This project will explore the effects of a new multicomponent program which includes cognitive-behavioral therapy sessions and outdoor adventure activities on affective and emotional variables, often affected in IPV victims. In addition, orientations to incorporate the main findings into the community based IPV resources and victims’ services will be provided.

## 1. Introduction

### 1.1. The Challenge of Violence Against Women

Violence against women is a major public health problem and a violation of women’s human rights [1]. According to the United Nations, there are different manifestations of violence against women such as intimate partner violence (IPV), sexual violence, or human trafficking, among others [2]. Specifically, IPV is committed by a current or former intimate partner, being the most common form of violence against women [3], and includes physical violence, sexual violence, stalking, or psychological harm [1,4].

Even though there are differences in the prevalence of violence depending on the region, globally almost one out of three women aged 15 and over have experienced physical and/or sexual IPV in their lives [5]. In Europe, studies performed by the European Union Agency for Fundamental Rights [6] showed that 22% of women over 15 years involved in a romantic relationship have experienced physical and/or sexual violence from their partner. In Spain, 32.4% of women older than 16 have experienced any kind of violence from their current or former partner in their lifetime and focusing on the last year 10.8% of women have experienced any kind of IPV [7]. In Extremadura, the Spanish region where the study will take place, 9% of women experienced any kind of intimate partner violence in the last 12 months [7]. During 2020, the Spanish Government Office against Gender-based Violence in its Statistical Portal (see http://estadisticasviolenciagenero.igualdad.mpr.gob.es (accessed on 22 March 2021)) reported that 45 women have lost their lives at the hands of their partners. Since 1 January 2003, a total of 1083 women have been murdered in Spain (updated 22 March 2021).

### 1.2. Psychological Consequences of IPV

The consequences of IPV on women’s health are multiple and well known [8], death being the most severe consequence. García-Moreno et al. [3] concluded that 38% of murdered women were killed by their intimate partner. Other consequences are health and psychosocial impacts. Dutton et al. [9] described how psychological, biological, neurological, behavioral, and physiological alterations were associated with posttraumatic stress disorder (PTSD) among IPV victims, leading to neuropsychological impairments [10]. Following ICD-11 criteria (International Classification of Diseases-11 [11]), PTSD and Complex PTSD (CPTSD) might appear as a consequence of women exposure to repetitive IPV and they could re-experience in the future such traumatic events in the present, in the form of vivid intrusive memories, flashbacks, or nightmares. The study carried out by Woods [12] showed high prevalence of PTSD symptoms in abused women. In this regard, women who have suffered IPV have more severe health problems compared with women who have not experienced violence from their partners [3]. Emotional consequences in IPV victims include slower healing compared to physical injuries [13], usually presenting reduced self-esteem [14], self-efficacy [13], body image [15,16], and damaged self-concept [17]. IPV female victims usually have higher prevalence of depression [18].

Suffering IPV often affects the way people see themselves. Focusing on the affective dimension, abused women have lower self-esteem compared to non-abused women [19]. In Tariq’s words “the self-esteem of the victim is completely crushed so much so that she lacks the confidence to preserve autonomy” [19] (p. 30) In relation to the cognitive component of self-esteem, studies have shown how IPV affects self-concept [20]. Penado Abilleira and Rodicio-García [20] concluded that suffering IPV affects the affective self-concept which ultimately leads to a damaged physical self-concept. Moreover, analyzing the different dimensions of the self-concept, female psychological victimization leads to lower academic and familiar self-concept [17].

IPV Victims often report poor physical self-concept, which is included in the Battered Women’s Syndrome as a condition within PTSD [21]. Body image is negatively affected by experiencing sexual [22] and physical abuse [16]. Empirical studies have found that IPV victims with violence-related injuries experienced higher body image concerns, which are a predictor of depressive symptoms [16]. IPV also affects women’s emotional appraisal regarding their body image, because psychological violence involves attacks and insults towards the victim’s body image, leading to feelings of shame toward their body [23].

IPV not only negatively affects women’s image, but also women’s belief in their own ability to successfully execute behaviors to reach their desired outcomes, that is, their self-efficacy [24]. Self-efficacy is crucial to explain IPV female victims’ individual differences in their recovery [25,26]. Previous studies have shown that self-efficacy is negatively affected by IPV [13] and lower levels of self-efficacy are associated with more severe symptoms of depression among IPV victims [26]. Lastly, studies in different countries have shown that IPV victims have higher levels of depression compared to non-victims [27,28].

### 1.3. Psychological Interventions for IPV Victims

Given the negative psychological outcomes described above, it is necessary to test the effectiveness of psychological interventions for IPV victims. Interventions have been carried out in shelters, prenatal clinics, or in the community [29]. We might distinguish between individual and group therapy for battered women. Whereas individual therapy, like cognitive trauma therapy for battered women with PTSD (CTT-BW), is helpful to restore self-esteem and reduce depression levels [30], group intervention has shown to be effective and the most common form of treatment [31]. Group interventions are mainly based on psychoeducational/supporting groups, cognitive and feminist approaches. Psychoeducational and supportive groups have revealed improvements in self-esteem [32,33] and depression [34]. Moreover, Santos et al. [31] demonstrated how a cognitive-behavioral orientation group intervention could improve self-esteem and depression levels in IPV women. Through a group intervention using psychoeducation and cognitive restructuring among other techniques, authors described a reduction of social isolation, clinical symptomatology, and an improvement on self-esteem [31]. In Spain, Santandreu-Oliver et al. [35] highlighted the effectiveness of a weekly ten-sessions group intervention focused on self-concept and self-esteem enhancement. These authors [35] developed an intervention addressing self-concept, cognitive distortions, pathological criticism, positive thinking, goal setting and psychological manipulation identification, in which self-esteem was the core component.

Other types of intervention have been suggested from different disciplines. In this regard, the connection with nature may be an alternative and a complementary approach to arrive at psychological benefits among people with different medical and psychological conditions [36]. Concerning IPV victims, the American Psychological Association, in their guidelines for psychological practice with women [37], recommended the use of wilderness therapy with abused women. This type of therapy encompasses individual and group therapy in natural settings and includes outdoor programs in the wilderness with personal growth, therapeutic, rehabilitation, education, and/or leadership development purposes [38]. The definition of wilderness therapy is closely related to, or even synonymous, with other concepts, such as adventure therapy or wilderness adventure therapy, among others [39]. Bowen and Neill [39] in a meta-analysis concluded that wilderness therapy programs were effective in short and long-term behavioral, emotional, and interpersonal outcomes [39]. Scant research has explored the role of wilderness therapy among IPV victims. An exception is the study carried out by McBride and Korell [40], who described a wilderness retreat for abused women. Although authors did not assess the effectiveness of the intervention on self-esteem or self-concept, they explained how wilderness therapy might create the opportunity to foster personal empowerment among IPV victims. Moreover, Reizvikh [41] tested informal nature therapy with victims of interpersonal violence, highlighting the importance of including a new way of trauma treatment among domestic violence victims. Levine [42], working with a group of sexually abused women, concluded that wilderness therapy helped the victims to deal with body image concerns and self-imposed limitations.

### 1.4. Aim

It is well known that cognitive-behavioral psychological multicomponent programs are the gold standard for the treatment of a wide variety of psychological problems [43]. This kind of treatment program, applied both individually and in groups, is characterized by the combination of several techniques (components) which aims to address the multiple factors involved in the origin and maintenance of specific psychosocial problems. Such modalities of treatment have previously shown their efficacy when compared with individual components and represent a traditional therapeutic approach with solid empirical support (e.g., [44,45]). To our best knowledge, no published research has explored the effects of a multicomponent intervention program to treat self-esteem and self-concept in IPV victims across an outdoor program in a natural, real setting. This project aims to analyze the effects of a multicomponent intervention program on self-esteem in IPV victims. Additionally, secondary aims include assessing the impact of the intervention on self-concept, body image, self-efficacy, and depressive symptoms. Taking into account the objectives explained above, we have designed a multicomponent program based on an indivisible combination of psychological and adventure components which are encompassed as a single approach. Based on the findings identified in the scientific literature and reported above, we hypothesize that, compared with the control group, women in the experimental group will enhance their self-concept, self-efficacy, and self-esteem while reducing their depressive symptoms and their body image concerns. 

## 2. Materials and Methods

### 2.1. Study Design

A single-blinded randomized controlled pilot trial will be conducted following the guidelines collected in The Consolidated Standards of Reporting Trials Statement (CONSORT) methodology for randomized controlled trials [46].

### 2.2. Ethics Approval

The Bioethics and Biosafety Committee at the University of Extremadura approved the performance of this trial (approval number: 187/2020). This study has been registered in the ISRCTN Clinical Trials Registry recognized by the World Health Organization (WHO) and the International Committee of Medical Journal Editors (ICMJE) (Trial number: ISRCTN14216182).

### 2.3. Randomization and Blinding

Randomization and blinding procedures will be conducted after inclusion and exclusion criteria have been verified. Participants will be assigned to one of the groups: experimental (multicomponent program) or control. A research team member who will not be directly involved in the trial will create a simple computer-generated randomization sequence using the software Research Randomizer (Version 4.0, Urbaniak G.C. and Plous S., Middletown, CT, USA; http://www.randomizer.org (accessed on 22 June 2013) [47]). The assignment will be hidden with a password-protected file. The researchers involved in the data analysis processes will not be aware of the group to which each woman will be assigned (experimental or control).

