### 2.5. Sample Size

The sample size was calculated using data from previous studies. First, we considered the mean and standard deviation of the Rosenberg Self-Esteem Scale (Spanish version of Fernández-Montalvo & Echeburúa [48]) used in females who were victims of intimate violence and participated in the study carried out by Santandreu-Oliver et al. [35]. Because there were no similar studies using wilderness therapy to improve self-esteem in IPV victims, the expected improvement was set based on the results from the above-mentioned study [35] where enhancements were slightly higher than 10%, and in the study performed by Santos et al. [31] where the improvements were slightly higher than 20%. Thus, the estimated change was set at 15%. A minimum of 17 participants per group (34 in total) would be needed to detect differences of at least 15% with a power of 80% and an α value of 0.05 [49].

Experimental group: participants will attend a multicomponent program which will include: (1) participation in cognitive-behavioral group-based therapy and (2) outdoor adventure activities in the Valle del Jerte. They will continue participating in their daily activities and usual treatments. The intervention program will be composed of eight sessions that will take place over the weekends. Each session will include both psychological and adventure components. The first part of each session will address the psychological component (e.g., group cohesion and behavioral contract) that will prepare the participants to develop the adventure activity, and the second part will be the adventure sport activity itself (e.g., adventure and multi-adventure pedagogy). All the sessions will be driven and supervised by professionals in the field. During the activities with the psychological component, an IPV specialized psychologist will work on self-concept and will prepare women for the activity to be carried out. The second part of the session will be led by experts in sport sciences with additional ongoing psychological support from the therapist. The sessions comprising the multi-component program are detailed in Table 1.

Control group: participants included in the control group will be encouraged to continue receiving their usual treatment care. Women assigned to the control group will be assessed like those included in the experimental group, taking into account the same psychological and social variables at pre-treatment, post-treatment, and at 1- and 3-months follow-ups.

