Regarding limitations, it should be noticed that all the women will be from the autonomous community of Extremadura, so cultural differences could affect the generalization of the results, so further studies will be needed to confirm the results and make them generalizable to women from other regions. Participants in both groups will be encouraged to continue with their usual activities and will be provided with a referral card enlisting IPV community resources, which could affect the results due to the potential heterogeneity of the therapies in which women are usually enrolled. Moreover, this study is based on a short and heterogenous sample design in which we do not intend to distinguish whether women have suffered psychological violence exclusively, or physical violence too. We are aware that our study comprises a small sample size, which could impose a limitation if there were a loss of participants, considering the duration of intervention and the need to travel to perform experimental group activities. Nevertheless, sample size calculations indicated that the sample is enough to achieve a statistical power over 80%. Another limitation is the failure to control for potential comorbidities (e.g., anxiety disorders, PTSD), and this should be addressed on future studies. It should also be noted that, although we have grouped IPV women into a single group, their heterogeneity in terms of type, frequency, severity, and chronicity of the violence is great. Despite these limitations, the current study protocol summarizes the first randomized controlled pilot trial involving psychological and adventure components aimed to enhance the emotional skills of women who were victims of IPV.

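### The simple randomization sequence named in section 2.3 does not, in its standard meaning, deliver the 17:17 allocation the plan states; the power cost is small and the fix is one line

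*Protocol article*

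**What the plan says.** Section 2.3 (Randomization and Blinding) says that a team member not directly involved in the trial "will create a simple computer-generated randomization sequence using the software Research Randomizer". The allocation is kept in a password-protected file. No block, stratum or fixed arm size is mentioned.

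The Abstract states the intended result: "34 IPV female victims will be recruited and equally assigned to the experimental" or the control group, with n = 17 in each.

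Section 2.5 (Sample Size) ties the calculation to that split: "A minimum of 17 participants per group (34 in total) would be needed" to detect a 15% difference, "with a power of 80% and an α value of 0.05". Of its inputs it says only that "we considered the mean and standard deviation of the Rosenberg Self-Esteem Scale" from an earlier study; neither value is printed.

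The Discussion says that the sample gives power above 80%. It also calls the small sample size a point "which could impose a limitation if there were a loss of participants".

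**The concern.** The article names a method and, elsewhere, a result that this method does not guarantee. A simple sequence is ordinarily an independent coin toss for each participant, so arm sizes are random. The total of 34 is exactly twice the stated minimum of 17, so there is no surplus: any split other than 17:17 leaves one arm below the plan's own minimum.

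Two things are at stake. One is consistency: someone who follows section 2.3 literally will usually not obtain the allocation in the Abstract and section 2.5. The other is precision, because an unequal split of a fixed total gives a somewhat less precise comparison, and a smaller arm has less room for the losses that the Discussion already worries about.

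**Working it through.** **Inputs.** Total 34, planned 17 per arm (Abstract, section 2.5). Power 80%, alpha 0.05 (section 2.5). Simple sequence (section 2.3), taken as independent 1:1 allocation. Sidedness is not stated, so two-sided is assumed.

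**1. The plan's own figure.** The 17 per group cannot be recalculated forward, because the mean and SD are not given. It can only be inverted. For a two-sided two-sample t-test with 17 per arm, 80% power requires a standardized difference d = 0.991 (0.961 with the normal approximation). A 15% change then corresponds to an SD of about 15/0.991 = 15.1% of the reference mean. A one-sided test would give d = 0.871. The value d = 0.991 is therefore an assumption made for step 4, not a figure from the article.

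**2. Distribution of the split.** With X the number in the experimental arm, X ~ Binomial(34, 0.5).

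P(17:17) = C(34,17)/2^34 = 2,333,606,220 / 17,179,869,184 = 0.136. So P(one arm below 17) = 1 − 0.136 = 0.864.

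**3. Loss of precision, without assuming d.** With equal SDs, the variance of a difference in means is proportional to 1/n1 + 1/n2 = 34/(n1·n2). Relative to 17:17 it rises by the factor 289/(n1·n2). At 14:20 this is 289/280 = 1.03; at 12:22 it is 289/264 = 1.09.

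**4. Power at each split.** Noncentral t with 32 degrees of freedom and noncentrality d/√(1/n1 + 1/n2), with d = 0.991. At 17:17 this is 0.991/0.343 = 2.89; at 14:20, 0.991/0.348 = 2.84; at 12:22, 0.991/0.359 = 2.76.

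| Split (either direction) | P(exactly this) | P(this or more unequal) | Power |
|---|---|---|---|
| 17:17 | 13.6% | 100% | 80.0% |
| 16:18 | 25.7% | 86.4% | 79.9% |
| 15:19 | 21.6% | 60.8% | 79.5% |
| 14:20 | 16.2% | 39.2% | 78.7% |
| 13:21 | 10.8% | 22.9% | 77.7% |
| 12:22 | 6.4% | 12.1% | 76.4% |
| 11:23 | 3.3% | 5.8% | 74.6% |

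Weighting power by the probability of each split gives an average of 78.8%.

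**5. With a restricted list.** A random permutation of 17 + 17 labels gives 17:17 with certainty once all 34 women are randomized, and the power stays at the planned 80%.

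**The case against.** The strongest reply is that *simple* may be an ordinary adjective here. A plain computer-generated list with arm sizes fixed at 17 would satisfy section 2.3, the Abstract and section 2.5 together. The article is also condensed, and details of list generation are often left to the full protocol. This stands as a possibility: on that reading the allocation is sound and only the wording is at fault. It does not remove the point. The article does not say that sizes are fixed, and the word it uses is the technical term for unrestricted allocation.

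The second reply is that the consequence is slight, and this largely stands. The 86% chance of missing 17:17 includes 16:18, which costs about 0.1 percentage point of power. Splits no worse than 14:20 occur 77% of the time (100% − 22.9%) and cost at most 1.3 points. A loss of more than 3 points needs 12:22 or worse, about a 12% chance.

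The third reply is that the planned analysis is a repeated-measures ANCOVA adjusted for age and baseline (section 2.7), so t-test power does not describe it exactly. That is right. The power figures show the size of the loss under the back-solved assumption and are not a forecast for the planned model.

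**Conclusion.** The point holds as an inconsistency of modest consequence. In its standard meaning, the method named in section 2.3 gives the stated allocation only 13.6% of the time and produces 20:14 or worse 39% of the time. Average power is about 78.8% against 80%, assuming a two-sided t-test and d = 0.99 inferred from 17 per group. The probabilities depend only on the total of 34 and on reading *simple* as unrestricted.

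A reader might infer three stronger things that the article does not support:

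- **That the sample size fails.** The total of 34 is not contradicted, only the per-group figure, and power falls little under moderate imbalance.
- **That the comparison is biased.** Unequal arms arising by chance from simple randomization do not bias it.
- **That an excess of women in the experimental arm would disrupt the group programme.** The article gives no maximum group size, staffing ratio or other limit against which to judge this.

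It is worth correcting because the documented method and the documented result should agree, and because the correction is so cheap.

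**What to change.** In section 2.3, replace *simple* with a restricted 1:1 method that closes at 17 per arm. Either of these would do:

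- a concealed random permutation of exactly 17 experimental and 17 control labels;
- permuted blocks whose sizes sum to 34, for example four blocks of 4 and three of 6 in random order (4 × 4 + 3 × 6 = 34).

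Blocks of random size that are merely cut off at the 34th woman are not enough, because the last block may be unfinished. If a fixed-size list was already intended, state that and remove the word *simple*.

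The same uninvolved team member can prepare the list and hold it in the same password-protected file. Before enrolment the cost is essentially nil. One point needs care: with fixed arm sizes, the last assignments can be predicted by anyone who has followed all the earlier ones, so the list must stay concealed from those who enrol.

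The alternative is to keep unrestricted randomization, drop the promise of equal arms and recruit more. With 44 women there is a 90% chance of at least 17 in each arm, at the price of 10 additional participants.
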